## Abstract

**Background:**

Because of the short half-life of non-vitamin K antagonist oral anticoagulants (NOACs), consistent drug adherence is crucial to maintain the effect of anticoagulants for stroke prevention in atrial fibrillation (AF). Considering the low adherence to NOACs in practice, we developed a mobile health platform that provides an alert for drug intake, visual confirmation of drug administration, and a list of medication intake history. This study aims to evaluate whether this smartphone app-based intervention will increase drug adherence compared with usual care in patients with AF requiring NOACs in a large population.

**Methods:**

This prospective, randomized, open-label, multicenter trial (RIVOX-AF study) will include a total of 1,042 patients (521 patients in the intervention group and 521 patients in the control group) from 13 tertiary hospitals in South Korea. Patients with AF aged ≥19 years with one or more comorbidities, including heart failure, myocardial infarction, stable angina, hypertension, or diabetes mellitus, will be included in this study. Participants will be randomly assigned to either the intervention group (MEDI-app) or the conventional treatment group in a 1:1 ratio using a web-based randomization service. The intervention group will use a smartphone app that includes an alarm for drug intake, visual confirmation of drug administration through a camera check, and presentation of a list of medication intake history. The primary endpoint is adherence to rivaroxaban by pill count measurements at 12 and 24 weeks. The key secondary endpoints are clinical composite endpoints, including systemic embolic events, stroke, major bleeding requiring transfusion or hospitalization, or death during the 24 weeks of follow-up.

**Discussion:**

This randomized controlled trial will investigate the feasibility and efficacy of smartphone apps and mobile health platforms in improving adherence to NOACs.

**Trial registration:**

The study design has been registered in ClinicalTrial.gov (NCT05557123).

## Introduction

For the management of patients with atrial fibrillation (AF), stroke prevention with oral anticoagulants is central to guideline-recommended management (1–3). Previous large randomized controlled trials for AF have demonstrated improved safety and comparable effectiveness of non-vitamin K antagonist oral anticoagulants (NOACs) compared with warfarin (4–8). Also, in contrast to warfarin, NOACs have minimal drug or food interactions and predictable effectiveness with fixed dosing without the need for laboratory monitoring. Because of these benefits, NOAC use is expanding globally (9, 10), and the current guidelines favor NOACs over warfarin for stroke prevention in AF (1, 2).

However, there are issues with the relatively short half-life of NOACs. When doses are missed, there is a higher risk of a prothrombotic state (11). Therefore, during NOAC therapy, constant medication compliance is crucial to sustain the anticoagulation's effect on stroke prevention (12, 13). Failed persistence or poor drug adherence to NOACs may increase the risk of stroke, which may result in rising overall health care costs (14–17).

Recently, Desteghe et al. showed that telemonitoring with or without feedback resulted in higher NOAC adherence (18). However, monitoring and feedback by health care providers have high costs and require more infrastructure and manpower and, thus, are challenging to incorporate in an actual clinical setting. Currently, smartphones are available to most of the general population at affordable costs. With the advent of mobile technology and advances in artificial intelligence (AI), mobile-based feedback algorithms may be promising strategies to improve medication adherence with easy distribution (19). Although there are some debates over their efficacy, smartphone applications (apps) are currently acknowledged as an effective method for improving drug adherence (20–28). Smartphone apps can transmit push alarms or notifications to remind the patient to take their medication, which may function to increase drug adherence (29). There are some previous studies regarding mobile apps for improving drug adherence of NOACs (30, 31). However, these studies had a small number of participants and limited application functions. Considering the low drug adherence of NOACs in patients with AF in the real world (13, 17, 32), we developed a mobile health platform to provide an alert for drug intake, visual confirmation of drug administration, and a list of medication intake history. This study aims to evaluate whether this smartphone app-based intervention will increase drug adherence compared with usual care in a large population of patients with AF requiring NOACs.

## Methods and analysis

### Study design

The ReInforcement of adherence Via self-monitoring app Orchestrating biosignals and medication of RivaroXaban in patients with Atrial Fibrillation and co-morbidities (RIVOX-AF) study is a prospective, randomized, open-label, nationwide, multicenter trial to evaluate the efficacy of smartphone apps (MEDI-app) in improving drug adherence to NOACs in patients with AF. Thirteen tertiary university hospitals in South Korea will participate in this study. Enrollment began in March 2022, is currently ongoing, and is expected to be completed in late 2023. The study design has been registered at ClinicalTrials.gov (NCT05557123).

### Study population

We will enroll patients with AF aged 19 years or older with one or more comorbidities, including heart failure, myocardial infarction, stable angina, hypertension, or diabetes mellitus. Patients can be enrolled 3 months after myocardial infarction or percutaneous coronary intervention. Rivaroxaban (Rivoxaban, Samjin Pharm, Seoul, Korea) will be administered to the participants at an open-label dosage of 20 mg once daily. Patients using other NOACs can be enrolled after swiching to Rivoxaban. The dosage will be reduced to 15 mg or 10 mg once daily if creatinine clearance is 15–49 ml/min or at the physician's discretion. Since smartphone usage is essential in this study, participants should be proficient in the use of smartphones and be able to understand and follow Korean instructions for using the program. Patients with severe chronic kidney disease (creatinine clearance <15 ml/min), moderate or severe mitral valve stenosis, or a history of mitral valve replacement or repair will be excluded. The detailed inclusion and exclusion criteria are listed in Table 1.

**Table 1 T1:** Inclusion and exclusion criteria.

** *Inclusion criteria:* **
1. Patients with AF aged 19 years or older with one or more comorbidities including heart failure, myocardial infarction, stable angina, hypertension or diabetes mellitus (Patients can be enrolled 3 months after myocardial infarction or percutaneous coronary intervention). 2. Patients with AF who are taking or initiating newly-prescribed rivaroxaban 3. Patients who can use a smartphone and are fluent in Korean 4. Patients who voluntarily consent to participate in this clinical trial
** *Exclusion criteria:* **
1. Creatinine clearance less than 15 ml/min 2. Moderate or severe mitral stenosis 3. Previous history of mitral valve replacement or mitral valve repair 4. Previous history of alcohol or drug abuse 5. Patients who are judged as both legally and psychologically inadequate to participate in the clinical study by the investigator 6. Patients who have participated in clinical studies with other investigational drug products within 4 weeks prior to screening 7. Patients unwilling to participate in the clinical study

AF, atrial fibrillation.

At baseline, sex, age, and comorbidities will be evaluated in all participants. The CHA_2_DS_2_-VASc score for stroke risk prediction will be calculated by the summation of all assigned points: one point each for congestive heart failure (C), hypertension (H), age between 65 and 74 years (A), diabetes mellitus (D), vascular disease (V), and female sex (Sc) and 2 points each for a history of stroke/transient ischemic attack/thromboembolism (S_2_) or age ≥75 years (A_2_) (1, 33).

### Patient recruitment and randomization

Any patient who comes to the clinic for AF management will be considered a potential participant. After a comprehensive interview, eligible participants will be asked to provide written consent for participation in the trial. A baseline survey covering demographics and cardiovascular comorbidities will be given to eligible participants (Table 2). These data will be collected by a research nurse, who will re-interview the patient and refer to the doctor's notes. Then, using a web-based central randomization service (http://matrixmdr.com), eligible participants will then be randomly assigned to either the intervention group (MEDI-app) or the conventional treatment group in a 1:1 ratio. It will not be possible to blind the participants to group allocation owing to the nature of the intervention.

**Table 2 T2:** Standard protocol items: Recommendation for interventional trials (SPIRIT) check list.

	STUDY PERIOD			
	Enrolment	Allocation	Post-allocation	Close-out
TIMEPOINT	Day -28 to 0	Visit 1 (day 0)	Visit 2 (12 weeks)	Visit 3 (24 weeks)
ENROLMENT:				
Eligibility screen	X			
Informed consent	X			
Allocation		X		
INTERVENTIONS:				
Intervention (MEDI-app)		♦——————————————————————————♦		
Control (Conventional Treatment)		♦——————————————————————————♦		
ASSESSMENTS:				
Baseline characteristics	X			
Drug adherence		X	X	X
Secondary endpoints			X	X

### Intervention (smartphone app-conditioned feedback) and follow-up

We developed a mobile application (MEDI-app) to improve NOAC adherence in patients with AF. Participants in the intervention group will install the study app provided by a research nurse on their smartphones (Figure 1). Because the app is not an open application available to the public, the control group cannot access the application. The workflow, operating system, and display of the smartphone application are shown in Figures 1, 2. The patient can use facial recognition to log in to the app (Supplementary Figure S1). The design, development, and utilization details of the physician-oriented web and patient-oriented smartphone app are described in the online Supplementary material.

**Figure 1 F1:**
[figure not shown]
System architecture and structural workflow.

**Figure 2 F2:**
[figure not shown]
Operating system and sample display of the smartphone app. Workflow of facial login, medication recognition, action recognition, and drug adherence are shown.

The research coordinator will enter the information on rivaroxaban administered to the patient into the mobile application and will set the alarm initially. The participants will be able to change the time of the alarm for rivaroxaban. When the alarm sounds at a pre-specified time, the patient will be reminded to take rivaroxaban. The app also determines whether the patient takes the medication through medication and action recognition software (Supplementary Figure S2). To elaborate, the first step is medication recognition, which determines whether the patient is taking the correct pill. A deep learning model of medication recognition will be exported after the completion of the training phase to perform real-time inference on the server from a picture captured by the camera on the patient's smartphone to match the name, shape, and color of the pill. In the second step, the app will visually confirm if the patient has taken the pill through action recognition via the smartphone camera by watching the patient put the medicine into their mouth through the camera.

If the patients do not confirm taking the medication at the scheduled time, the app will send an alert message to ensure that the patients take the medicine until 2 h after the set drug intake time. If the patient does not comply with the pill intake procedure within these 2 h, it is assumed that the patient did not take the pill, and the app will send non-intake data to the server accordingly. As an alternative, patients can also confirm that they have taken the medicine by pressing the intake button within a day, rather than using action recognition via the camera. This information can be updated on the server. Data regarding the time of rivaroxaban intake will be stored daily, and patients can check the list of drug adherence per week or month on a calendar through the app. The dashboard system is designed to show the physicians the history and number of days that the participants confirmed taking their medication (Supplementary Figure S3). In this study, the app will be initially configured only for the rivaroxaban dose, frequency, and pill supply.

The control group will receive only standard care which is recommended in the guidelines, including education on the disease and the importance of medication compliance by physicians at each scheduled visit. No other specific interventions will be performed. Follow-up visits will be scheduled at 12 (visit two) and 24 (visit three) weeks after randomization (Figure 3).

**Figure 3 F3:**
[figure not shown]
Study design of RIVOX-AF. Patients taking rivaroxaban will be randomized to either an application-conditioned feedback group or a conventional treatment group. Follow-up visits will be scheduled at 12 (visit two) and 24 (visit three) weeks after randomization.

### Study outcomes

The primary endpoint of the study is adherence to rivaroxaban at 12 and 24 weeks. Drug adherence will be evaluated with the “pill count” measurements. The patients brought the remaining tablets to each scheduled visit, and trained and certified research nurses counted the number of returned drugs and calculated drug adherence as follows:$$\begin{array}{rl} & \mathrm{Drug}\;\mathrm{adherence}\;=\\ & \frac{\mathrm{number}\;\mathrm{of}\;\;\mathrm{pills}\;\mathrm{dispensed}-\mathrm{number}\;\mathrm{of}\;\mathrm{pills}\;\mathrm{returned}}{\mathrm{number}\;\mathrm{of}\;\mathrm{days}\;\mathrm{between}\;\mathrm{dispensing}\;\mathrm{date}\;\mathrm{and}\;\mathrm{follow}-\mathrm{up}\;\mathrm{date}} \end{array}$$In addition, we will evaluate the concordance of drug adherence by pill count measurements and app-calculated indices.

The key secondary endpoints are clinical composite endpoints, including systemic embolic events, stroke, major bleeding requiring transfusion or hospitalization, or death during the 24 weeks of follow-up. Other secondary endpoints include (1) major adverse cardiac and cerebrovascular events and hospitalization, (2) thromboembolism (stroke, transient ischemic attack, pulmonary embolism), (3) major bleeding requiring hospitalization or transfusion, or (4) minor bleeding. To evaluate the feasibility of the smartphone app, additional analysis will be conducted regarding the frequency of smartphone app use.

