### Sample size and statistical analysis

To date, no large studies have evaluated the use of a smartphone app to improve adherence to NOACs using pill count measurements. Thus, precise sample size calculation is not possible. We assumed that drug adherence would be 91% in the control group and 95% in the intervention group with a standard deviation of 17%, considering previous studies (30, 34, 35). With a two-tailed alpha of 0.05, power of 0.95, and a dropout rate of 10%, 1,042 patients (521 patients in the intervention and 521 patients in the control groups) are required.

Categorical variables will be reported as frequencies (percentages), and continuous variables will be expressed as means ± standard deviations or medians with interquartile ranges. Categorical variables will be compared using Pearson's chi-square test or Fisher's exact test, and continuous variables will be compared using Student's *t*-test or the Mann–Whitney *U* test.

Intention-to-treat analyses will include all randomized patients. Efficacy endpoints will be mainly analyzed using the full analysis set, which includes all randomly assigned participants who underwent at least one assessment of the primary endpoint. We will also perform a per-protocol sensitivity analysis, including all patients who completed the study protocol. In the subgroup analyses, we will evaluate the differential effects of the intervention on the primary outcomes with respect to sex, age and other comorbidities.

All tests will be two-tailed, and a *P*-value <0.05 will be considered statistically significant. Statistical analyses will be performed using R version 4.2.0 (The R Foundation for Statistical Computing, Vienna, Austria).

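### The primary endpoint names two visits with no lead visit, while the 0.05 rule and the sample size provide for only one comparison

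*Protocol article*

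**What the plan says.** In the protocol article, the Study outcomes section states: "The primary endpoint of the study is adherence to rivaroxaban at 12 and 24 weeks". The Methods paragraph of the abstract agrees: "The primary endpoint is adherence to rivaroxaban by pill count measurements at 12 and 24 weeks". Neither place says which visit leads, or whether success needs one visit or both.

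The section Sample size and statistical analysis assumes that "drug adherence would be 91% in the control group and 95% in the intervention group with a standard deviation of 17" per cent. This is one pair of means with no time point attached. It continues: "With a two-tailed alpha of 0.05, power of 0.95, and a dropout rate of 10" per cent, and arrives at 1,042 patients, 521 per arm. For continuous variables it names Student's t-test or the Mann–Whitney U test. Its closing rule is "All tests will be two-tailed, and a *P*-value <0.05 will be considered statistically significant". The full analysis set requires at least one assessment of the primary endpoint, so more than one assessment per patient is foreseen.

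The adherence formula in Study outcomes divides tablets dispensed minus tablets returned by the days from the dispensing date to the follow-up date. It does not say which dispensing date applies at week 24.

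**The concern.** Three elements that the article itself fixes do not fit together without a further rule: a primary endpoint at two visits, a 0.05 threshold for every test, and a sample size for one contrast. If a significant result at either visit counts as success, the trial has two chances of a false positive. If both visits must be significant, the chance of success under the planning assumptions is lower than the stated 0.95.

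What is at stake is which result decides the trial. Suppose the app improves adherence at 12 weeks and the effect fades by 24, or appears only late. The text would allow a positive primary claim in either case, chosen after the data are seen. In an open-label trial that choice is best closed in advance.

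**Working it through.** **Inputs from the protocol article (Sample size and statistical analysis; Patient recruitment and randomization).** Difference 95 − 91 = 4 points; SD 17 points; two-sided alpha 0.05; power 0.95; dropout 10%; allocation 1:1; 521 randomised per arm.

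**Assumptions not in the article.** The correlation r between the 12-week and 24-week test statistics is not given, so a range is shown. The same evaluable patients contribute at both visits, and under the alternative the 4-point difference is present at both.

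**Step 1: reproduce the plan's sample size.**
n per arm = 2 × (1.960 + 1.645)² × (17/4)² = 469.4, rounded up to 470.
With dropout: 470/0.9 = 522.2, so 523 per arm (1,046 in total) against the stated 521 (1,042). The gap is two patients per arm and is consistent with rounding, since 469/0.9 = 521.1. The stated figure is therefore that of one comparison at the full 0.05.

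**Step 2: power of one test.**
Evaluable n = 521 × 0.9 = 468.9, taken as 469 per arm.
Noncentrality = 4 / (17 × √(2/469)) = 3.603.
Power = Φ(3.603 − 1.960) = 0.950, as stated.

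**Step 3: two tests, each at 0.05.** The two statistics are treated as bivariate normal with correlation r. Family-wise error is the probability that at least one |Z| exceeds 1.960 under the null. Joint power is the probability that both exceed 1.960 when each has mean 3.603.

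| r | Error if either visit suffices | Power if both are required |
|---|---|---|
| 0 | 9.75% | 0.902 |
| 0.3 | 9.5% | 0.907 |
| 0.5 | 9.1% | 0.912 |
| 0.7 | 8.3% | 0.919 |
| 0.8 | 7.8% | 0.925 |
| 0.9 | 7.0% | 0.932 |
| 1 | 5.0% | 0.950 |

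At r = 0 the entries follow by hand: 1 − 0.95² = 0.0975, and 0.9498² = 0.902.

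**Step 4: split alpha, 0.025 per visit, either visit sufficient.** The critical value is 2.241. Power at one given visit is Φ(3.603 − 2.241) = 0.913. The power that matches an either-visit claim is the probability of winning at least once:

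| r | Family-wise error | Power to win on at least one visit |
|---|---|---|
| 0 | 4.9% | 99.3% |
| 0.5 | 4.7% | 97.4% |
| 0.7 | 4.3% | 96.1% |
| 0.8 | 4.0% | 95.3% |
| 0.9 | 3.6% | 94.1% |

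**The case against.** The strongest objection is that no sentence says each visit will be tested separately. The article speaks of one endpoint, and one endpoint measured repeatedly would also fit the definition of the full analysis set. The sentence on tests is general to all continuous variables, and the 0.05 line is a general closing statement. A lead visit, a joint model or a test order is often placed in an analysis plan, and that document is not shown. This stands as a limit: separate testing is an inference, and a stated joint analysis would resolve the point. It does not remove the point, because the two visits, the blanket threshold and the one-contrast sample size are all in the article, and applied together they do not deliver the stated error rate and power.

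A reader might infer more than the documents support, in three ways.

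- **That the stated 5% and 95% cannot both be true.** They can. Both hold if one visit or one overall measure is the primary contrast. The error rate also holds, with at least 95% power to win on one visit, under a 0.025 split with either visit sufficient, up to a correlation of about 0.8. The 0.913 in Step 4 is power at one given visit, not for the either-visit claim.
- **That tablets are re-supplied at week 12, so the 24-week value must cover weeks 12 to 24.** The article gives no dispensing schedule. It leaves open which interval is meant.
- **That the sample size was built for cumulative adherence over weeks 0 to 24.** Nothing ties the 91%, 95% and 17% to any visit or interval.

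It is also fair to say that the both-visits branch costs only two to five points of power, in a plan that itself calls its sample size imprecise. Pill counts in the same patients are probably positively correlated, so the top of the error range is unlikely.

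**Conclusion.** The point holds as an unresolved conflict within the article: its two-visit primary endpoint needs a decision rule that its single-comparison alpha and sample size do not supply. The inflation of error arises only if a win at either visit is accepted at an unadjusted 0.05. The loss of power arises only if both visits are required. Only one of the two would apply, depending on the rule.

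Both sizes rest on separate testing and on a correlation that the documents do not give; the power figures also assume the planned 4-point effect at both visits. Error returns to 5%, and joint power to 0.95, only at perfect correlation. The excess error is moderate, but it concerns the trial's main claim and can be removed at almost no cost.

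**What to change.** Before database lock, name one primary contrast at two-sided 0.05. Adherence at 24 weeks, or one overall measure over weeks 0 to 24, would each serve. State which dispensing date the week-24 calculation uses, so that the interval is fixed. Make the other time point secondary, tested only if the primary is significant. State also that the 4-point difference and 17% SD are taken to apply to the chosen measure; on that condition 1,042 patients, 5% error and 95% power stand.

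The cost is a sentence or two in the protocol and analysis plan, with no new patients or data. The downside is that an effect seen only at the non-primary time point can no longer support the primary claim.

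An acceptable alternative is 0.025 at each visit with either sufficient. It keeps at least 95% power to win on one visit up to a correlation of about 0.8 (94.1% at 0.9), if the 4-point effect is present at both visits.

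### The pill-count formula for the primary endpoint scores every tablet not returned as taken and has no ceiling, so a poor adherer can score 100% or more

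*Protocol article*

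**What the plan says.** Under Study outcomes, the article states: "The primary endpoint of the study is adherence to rivaroxaban at 12 and 24 weeks". The returned count depends on what patients carry to the clinic: "The patients brought the remaining tablets to each scheduled visit". Then "trained and certified research nurses counted the number of returned drugs and calculated drug adherence as follows", and a displayed equation follows. Its numerator is tablets dispensed minus tablets returned. Its denominator is the number of days between the dispensing date and the follow-up date. The equation shows no truncation and does not separate tablets taken from tablets otherwise gone. Study population gives an "open-label dosage of 20 mg once daily", with lower once-daily doses for some patients. One tablet per day is therefore the natural reading of the expected count, although tablets per dose and tablets per interval are not stated.

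Study outcomes also plans a concordance check between pill count and app-calculated adherence. The Intervention section says that controls have no access to the app. Limitations and strengths presents pill counting as a strength and does not mention that unreturned tablets are scored as taken.

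**The concern.** The formula measures tablets that have left the patient's possession or were not shown to the nurse; it does not measure tablets swallowed. The two agree only if every leftover tablet comes back. The error runs upward and is largest in patients who miss many doses, because they have the most tablets that can be lost, discarded or left at home. These are the patients in whom a reminder app has most room to work.

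The planned difference is only 4 points (91% against 95%), and the trial is open-label. If the habit of bringing packs back is the same in both arms, the formula tends to blur the contrast. If the habit differs, it can add to or subtract from the contrast. The concordance check cannot reveal the problem in controls, because they have no app record to compare with.

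**Working it through.** **Inputs from the article.** Formula: Study outcomes. Visits at 12 and 24 weeks, so a 12-week interval is 84 days: Intervention and follow-up. Means 91% and 95%, SD 17%, two-sided alpha 0.05, power 0.95, dropout 10%, 521 per arm: Sample size and statistical analysis.

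**Assumptions.** Tablet quantities, non-return rates and true adherence among non-returners are assumed, because the article gives none.

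**1. The plan's own figure.** n per arm = 2 × (1.960 + 1.645)² × 17² / 4² = 469.4. Taking 469 and dividing by 0.9 gives 521.1, which matches 521 per arm and 1,042 in total. (Rounding up to 470 first gives 523 per arm.) The sample size reproduces and is not in question here.

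**2. The formula on single patients, 84 days.**

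| Dispensed | Taken | Returned | Formula | True |
|---|---|---|---|---|
| 84 | 60 | 24 | 60/84 = 71.4% | 71.4% |
| 84 | 60 | 0 (24 lost) | 84/84 = 100% | 71.4% |
| 90 | 60 | 0 (30 lost) | 90/84 = 107.1% | 71.4% |

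The first two patients behave identically towards the drug and differ only in what they bring back. The third row needs a supply larger than the number of days. At exactly one tablet per day the maximum is 100%.

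**3. Equal non-return in both arms.** Suppose a share f of each arm, unrelated to adherence, returns nothing and scores 100%. The control mean becomes 100 − 9(1 − f), the app mean becomes 100 − 5(1 − f), and the difference is 4(1 − f). With 469 per arm and SD 17, the standard error is 17 × √(2/469) = 1.110, and power = Φ(difference/1.110 − 1.96).

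- f = 0: difference 4.0, power 95.0%.
- f = 10%: difference 3.6, power 90.0%.
- f = 20%: difference 3.2, power 82.2%.

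Holding the SD at 17 overstates the loss a little, because placing scores at 100 also narrows the spread. At f = 10% the control variance becomes 0.9 × 289 + 0.09 × 9² = 267.4, and the app variance 0.9 × 289 + 0.09 × 5² = 262.4. The standard error is then √((267.4 + 262.4)/469) = 1.063, and power is about 92%.

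**4. Unequal non-return.** If non-return differs by 5 percentage points and those patients score 100%, the shift in the difference is 0.05 × (100 − their true adherence).

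- True adherence 91%: 0.05 × 9 = 0.45 points.
- True adherence 60%: 0.05 × 40 = 2.0 points.

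The sign depends on which arm returns fewer packs.

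**The case against.** The best defence is that this is the conventional pill-count ratio in a condensed article. Rules on truncation and on packs not brought may stand in the full protocol, the analysis plan or the case report form. Nothing in the article says that packs not brought are entered as zero returned; such a patient may simply have no assessment. This stands in part, and the point does not rest on missing detail. It rests on the stated equation, which scores lost or discarded tablets as taken however packs not brought are recorded. Any rule that corrects this changes the equation.

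A reader might infer several stronger things that the document does not support:

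- **That the bias is as large as the whole planned effect.** If 10% of one arm truly adhere at 60% and score 100%, that arm's mean rises by 0.10 × 40 = 4 points. That is a shift in one mean, on assumed rates, and it cancels if both arms behave alike.
- **That the app arm will double-dose and be rewarded for it.** The Intervention section says that, if intake is not confirmed, "the app will send an alert message to ensure that the patients take the medicine". It also limits these alerts to two hours, offers an intake button and shows the intake history. Double dosing could as well fall as rise.
- **That home stock inflates scores.** Eligibility covers "Patients with AF who are taking or initiating newly-prescribed rivaroxaban", so some patients may hold tablets already. Using them leaves more study tablets to return, which lowers the score.
- **That medically ordered days off drug add to the overstatement.** They stay in the denominator and lower the score when those tablets come back: a 14-day hold gives 70/84 = 83.3%. That error runs the other way, and whether to exclude such days is a choice of estimand.

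Treating packs not brought as missing is also only a partial cure. If the true arm mean is 91% and the 10% who are dropped truly adhere at 60%, the rest average (91 − 6)/0.9 = 94.4%. The bias is then 3.4 points instead of 4.0.

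**Conclusion.** The point holds as a property of the stated formula: unreturned tablets count as taken, and nothing bounds the score at 100%. For a single patient the overstatement can be large (100% against 71.4% in the example). Scores above 100% are possible, but the article does not show that they will occur, since the dispensed quantity is not given.

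For the trial result, neither the size nor the direction of bias can be derived from the article. The illustrations give a moderate loss of power under equal non-return (95% to about 90% at 10% non-return with SD 17). Under a 5-percentage-point imbalance the shift is 0.45 to 2.0 points, the upper end being half the planned effect. They rest on the assumed non-return rates, on a score of 100% for those patients, and, for the power figures, on non-return being unrelated to adherence. The 1,042 patients are correctly derived from the stated inputs.

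**What to change.** Amend the endpoint definition before analysis:

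1. In the primary analysis, cap adherence at 100% per dispensing interval, and report by arm the proportion of intervals above 100%.
2. Record packs not brought separately from no tablets left. Do not enter the former as zero returned; treat that interval as missing.
3. Add a sensitivity analysis scoring those patients as non-adherent. It is needed because missing packs probably go with low adherence, so treating them as missing removes only part of the bias.
4. Handle documented, medically directed interruptions in a sensitivity analysis only.
5. State under Limitations and strengths that pill count cannot tell taken tablets from lost ones.

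The cap does not recover tablets that were lost or discarded; item 5 is the honest answer to that part.

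The cost is one paragraph and one tick-box on the visit form. Mean adherence will look slightly lower and some intervals will become missing. Enrolment was already under way when the article was written, so whether packs were brought may not be recoverable for patients already seen. The extent of that gap should be reported.
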